### Sample size and power

Group sample sizes of 73 in the experimental arm and 73 in the control arm achieve 80.3% power to reject the null hypothesis of equal mean changes in the HEI2015 total score when the population difference in mean change in the two arms is µ1 - µ2 = 5.5 with a standard deviation for both arms of 13.3 and with a significance level (alpha) of 0.05 using a one-sided two-sample equal-variance z-test. The standard deviation is derived based on work from our nonrandomized virtual nutrition education with cooking demonstrations pilot study data. We anticipate enrolling 90 participants per group to achieve this target sample size assuming ~ 20% drop out rate. This drop-out rate is consistent with our previous studies.

### Statistical methods

The primary analysis will assess within-subject change in HEI score (3-month minus baseline) using a paired samples t-test if assumptions of normality and equal variance are met. If the equal variance assumptions are violated, an unequal-variance t-test will be used. If the data are non-normal, an appropriate transformation or non-parametric alternative will be applied. Exploratory post hoc analyses will assess heterogeneity of treatment effect, with the hypothesis that dietary quality will improve in the nutrition intervention group compared to contact control. Covariates (age, race/ethnicity, sex, medical history/comorbidity, medications, education, living situation, and annual household income) will be included in negative binomial regression models, analyzing changes in outcomes from baseline to 3 months per participant. Although weight loss is not an intended outcome, we will measure how the intervention may change body composition (DEXA). The same modeling strategies (negative-binomial regression, multinomial, or linear mixed effects models) will be applied to each outcome using piecewise approach, with a change point occurring at 6 months to determine whether treatment effects differ or persist after this time. Finally, we will test whether continued participation in the virtual nutrition intervention after intervention completion moderates the persistent effect of the intervention on study endpoints. Missing data will be handled using an intention-to-treat approach with multiple imputations, with 5–10 imputations recommended to account for uncertainty in missing values and to produce valid, unbiased estimates of treatment effects [57]. No interim analysis are planned.

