**Methods:**

This randomized controlled trial will test whether a 12-week virtual nutrition and teaching kitchen program improves diet quality (Healthy Eating Index [HEI]), compared with time- and attention-matched contact-control group. We plan to enroll 180 Veterans *≥* 65 years of age with mobility limitations who will be randomized to an intervention or control group. Participants in the intervention group will attend one live, one-hour virtual session each week for 12 weeks, including cooking demonstrations, and tailored nutrition education, with adaptive equipment and occupational therapy guidance provided as needed. Control participants will attend matched group health education sessions focused on healthy aging. Outcome assessments occur at baseline, 3 months, and 6 months. The primary outcome is change in HEI score from baseline to 3 months. Secondary outcomes include change in HEI from 3 to 6 months, and changes in social isolation, loneliness, and health-related quality of life, physical function, body composition, and fear of falling from baseline to 3 months. Sample size calculations indicate that 73 participants per group will provide 80% power to detect a 5.5-point between-group difference in HEI, allowing for 20% attrition.

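### The primary analysis is written as a paired t-test of change from baseline, which does not compare the two randomised arms

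*Protocol article*

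**What the plan says.** The Statistical methods section defines the primary analysis in one sentence: "The primary analysis will assess within-subject change in HEI score (3-month minus baseline) using a paired samples t-test". The test is conditional on normality and equal variance, and the next sentence gives the fallback: "If the equal variance assumptions are violated, an unequal-variance t-test will be used". Neither sentence mentions arm, group or a contrast between groups.

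Within that section, the hypothesis of improvement relative to control appears only in a sentence about exploratory post hoc work on heterogeneity of effect: "with the hypothesis that dietary quality will improve in the nutrition intervention group compared to contact control". The covariate-adjusted models that follow are not called primary, and no treatment term is stated for them.

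Elsewhere the article is clear that the comparison is between arms. The abstract asks whether the programme "improves diet quality (Healthy Eating Index [HEI]), compared with time- and attention-matched contact-control group". The Sample size and power section sets out to "reject the null hypothesis of equal mean changes in the HEI2015 total score", using a two-sample z-test with a 5.5-point difference between arms.

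**The concern.** A paired t-test on 3-month minus baseline HEI tests whether the mean change is zero, either in one arm or in all participants together. It cannot separate the effect of the programme from anything that moves both arms. This trial has several candidates for such a shared change:

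- Everyone enrolled has indicated a wish to eat better.
- Everyone completes repeated 24-hour recalls.
- Both arms attend weekly live sessions.

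The contact control exists to remove these influences, and the stated primary test does not use it.

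The paragraph is also inconsistent within itself. A paired test has no equal-variance assumption, and an unequal-variance t-test is a two-sample procedure. Read literally, a variance check would decide whether the primary hypothesis is that mean change is zero or that the arms differ. At stake is an efficacy claim resting on a within-arm rise, or a choice between the two tests once the data are visible.

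**Working it through.** **Inputs.** The Sample size and power section gives 73 evaluable per arm, a difference in mean change of 5.5, an SD of 13.3 in both arms, and one-sided alpha 0.05. The article gives no expected change in the control arm, so the shared change used below (1 to 5 HEI points) is an assumption.

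**1. Reproduce the plan's figure.** For a two-sample z-test:

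- SE = 13.3 × √(2/73) = 2.201
- 5.5 / 2.201 = 2.498
- power = Φ(2.498 − 1.645) = Φ(0.853) = 0.803

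This matches the stated 80.3%. A two-sample t-test on the change scores (noncentral t, 144 df) gives 80.0%. The sample size was therefore derived for a between-arm test.

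**2. The paired test on the same inputs is a different test.** The n in one arm for 80% power to detect a 5.5-point change, one-sided 0.05, by the normal approximation is

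(13.3 × (1.645 + 0.842) / 5.5)² ≈ 36.2

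With 73 in one arm the power would be 96.8% (noncentral t). Neither figure resembles the stated design.

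**3. Error rate for the between-arm question.** Let the true treatment effect be zero and let both arms change by the same amount d. The paired test has noncentrality d/SE, where:

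- intervention arm alone: SE = 13.3/√73 = 1.557, 72 df
- both arms pooled: SE = 13.3/√146 = 1.101, 145 df

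Probability of a significant result at the 5% level:

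| Shared change d | One arm, two-sided | One arm, one-sided | Pooled, two-sided | Pooled, one-sided |
|---|---|---|---|---|
| 0 | 5% | 5% | 5% | 5% |
| 1 | 9.7% | 15.7% | 14.7% | 22.9% |
| 2 | 24% | 35.5% | 43.8% | 56.5% |
| 3 | 47.7% | 60.4% | 77.3% | 85.7% |
| 4 | 71.7% | 81.6% | 95.1% | 97.6% |
| 5 | 88.7% | 93.8% | 99.5% | 99.8% |

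A two-sample test of the change scores stays at 5% in every row, because the shared change cancels. Both sidedness conventions are shown because the Statistical methods section states none, while the power calculation is one-sided.

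**The case against.** The strongest reply is that this is a misnamed test and not a flawed design. The equal-variance condition, the unequal-variance fallback, the two-sample power calculation and the abstract all point to an independent-samples t-test on each participant's change score. That reading is the likeliest one, and I accept it as the probable intention. It does not remove the fault: the sentence that fixes the primary analysis names another test, and nothing else in the article corrects it. Nor is this a detail left to an analysis plan that is not shown. The article does state the primary test, and a plan naming a two-sample test would conflict with it.

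Four narrower objections have some force:

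- The between-arm aim is stated elsewhere in the article. It is only within the Statistical methods section that the hypothesis appears solely in the exploratory sentence, and that sentence may not have been meant to demote the main comparison.
- It would go too far to say that the control arm is certainly discarded, since the text does not limit the paired test to the intervention arm. Pooling the arms would not help, because it still contains no contrast.
- Regression to the mean is a weak argument here. Entry depends on a single self-rating of eating habits and not on a low HEI score. The concern does not need it, because any shared change is enough.
- The listed control topics are general healthy aging, while the nutrition teaching, cooking and produce go to one arm. The shared change could therefore be small, and the table shows how the error rate depends on it.

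**Conclusion.** The concern holds: the primary analysis is wrong as written. The stated test contains no comparison of the randomised arms. It contradicts both the trial's question and the hypothesis on which the trial was powered, and it does not fit its own variance conditions. If it were followed literally with no treatment effect, a shared rise of 2 to 4 HEI points would give a significant result in the intervention arm with probability 24% to 72% at two-sided 5%, or 44% to 95% with both arms pooled, against a nominal 5%. These rates rest on the plan's SD of 13.3, on 73 completers per arm, and on assumed shared changes for which the article gives no figure. The contradiction itself rests on no assumption. The randomised design and the data to be collected can answer the question once the test is corrected.

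**What to change.** Replace the primary analysis sentence. The primary analysis should estimate the difference between arms (intervention minus contact control) in mean 3-month change in HEI total score, from a linear model with a treatment term. All randomised participants are kept in their assigned arm, and the estimate is reported with a 95% confidence interval. Adjustment for baseline HEI would also be suitable.

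Three consequential edits belong with it:

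- Report paired within-arm changes as descriptive only.
- Move the hypothesis of improvement over contact control out of the exploratory post hoc sentence and attach it to the primary analysis.
- Use heteroscedasticity-robust (Welch-type) standard errors from the start, so that a variance check on the data no longer selects the test.

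State the sidedness of the primary test in the same sentence. With the one-sided 0.05 of the sample size section, 73 per arm still gives 80.3% (z) or 80.0% (t), so this correction needs no extra participants. If a two-sided 0.05 test were chosen, power would be 70.5% (z) or 69.9% (t), and 92 evaluable per arm would be needed for 80%.

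The cost is a wording change in the protocol and the analysis plan before any analysis, with no new data.

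### The observed data choose the primary test, and the non-normality branch leaves the difference in mean HEI change for which the trial is sized

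*Protocol article*

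**What the plan says.** In the protocol article, Statistical methods, the primary analysis is of each participant's HEI change (3 months minus baseline), "using a paired samples t-test if assumptions of normality and equal variance are met". Two fallbacks follow. For variance: "If the equal variance assumptions are violated, an unequal-variance t-test will be used". For shape: "If the data are non-normal, an appropriate transformation or non-parametric alternative will be applied".

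Sample size and power gives 73 per arm 80.3% power to "reject the null hypothesis of equal mean changes in the HEI2015 total score". The assumed difference in mean change is "5.5 with a standard deviation for both arms of 13.3", "with a significance level (alpha) of 0.05 using a one-sided two-sample equal-variance z-test".

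Statistical methods then adds: "Missing data will be handled using an intention-to-treat approach with multiple imputations, with 5–10 imputations recommended". It does not say whether the normality and variance checks are made on the observed data or on the imputed datasets.

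**The concern.** This is a rule that the article states, not a detail left to an unseen analysis plan. A plan that implemented it faithfully would inherit the difficulty.

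- **Target.** The trial is sized for a difference in means on the HEI scale. A rank test asks whether values in one arm tend to exceed those in the other. A transformed analysis compares means on another scale and does not return a difference in HEI points. Either may be a reasonable secondary question, but neither is the planned one.
- **Discretion.** Both the choice to leave the mean and the choice of where to go are made with the primary outcome data in hand.
- **Coherence.** A paired test works on a single column of differences, so there are no two variances to compare. The trigger for the variance branch does not belong to the test it qualifies.
- **Imputation.** If the checks are repeated in each imputed dataset, they can disagree within one trial. The usual combination rules pool an estimate and its variance, and a rank-test p-value supplies neither.

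**Working it through.** **1. The plan's own figure.** Inputs from Sample size and power: n = 73 per arm, difference 5.5, SD 13.3, one-sided alpha 0.05.

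- Standard error = 13.3 × √(2/73) = 2.201.
- 5.5 / 2.201 = 2.498, and 2.498 − 1.645 = 0.853.
- Power = Φ(0.853) = 80.3%. The stated figure reproduces, and it is for a two-sample comparison of means.

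**2. Does a fixed test of the mean cost power?** With the same inputs, a one-sided two-sample t-test on 144 degrees of freedom has 80.0% power, against 80.3% for the z-test. With equal arm sizes the unequal-variance t statistic equals the pooled one, so the unequal-variance form is practically the same. Sample size does not depend on the selection rule.

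**3. How the rank branch changes the target.** An assumed example: 25% of one arm change by +18 on average and 75% by −6, with SD 8.3 within each group. The other arm is normal with mean 0 and SD 13.3.

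- Mean: 0.25 × 18 − 0.75 × 6 = 0, so mean changes are equal.
- Variance: 8.3² + 0.25 × 18² + 0.75 × 6² = 68.89 + 81 + 27 = 176.89 = 13.3², so SDs are equal too.
- SD of the difference between one value from each arm, within each group: √(68.89 + 176.89) = 15.68.
- Chance that a value from the first arm exceeds one from the second: 0.25 × Φ(18/15.68) + 0.75 × Φ(−6/15.68) = 0.25 × 0.874 + 0.75 × 0.351 = 0.482.

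The equal-means null is true, while the rank test's null value of 0.5 is not.

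**4. Size of the effect on error rates.** The article names no diagnostic, so one was assumed: Shapiro-Wilk at 5% on pooled residuals, then Levene's test at 5%, leading to the pooled t, unequal-variance t or Mann-Whitney test. The default branch was read as a two-sample test on change. Each row has 4,000 simulated trials with 73 per arm, equal true mean change and two-sided 5% tests. Simulation standard error is about √(0.05 × 0.95 / 4000) = 0.3 points.

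| Shapes in the two arms | Fixed unequal-variance t | Selection rule | Mann-Whitney always |
|---|---|---|---|
| Both normal | 5.0% | 5.0% | 5.1% |
| Same skew in both | 5.0% | 5.4% | 5.1% |
| Skew against normal | 5.2% | 6.0% | 6.4% |
| Mixture of step 3 against normal | 5.3% | 6.4% | 7.6% |

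The excess of the rule over the fixed test is about 1 point, and only in the last two rows. These runs are two-sided, whereas the plan's sizing is one-sided. Which direction is favoured depends on which arm has the longer tail.

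**5. Disagreement if the checks are run in each imputed dataset.** Of 90 per arm, 20% (18) are missing and 72 observed. Entries are the share of trials in which Shapiro-Wilk at 5% gave different verdicts across the imputed datasets of the same trial.

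| Check and data | 5 imputations | 10 imputations |
|---|---|---|
| Pooled residuals, normal | 13% | 20% |
| Pooled residuals, gamma shape 16 (skewness 2/√16 = 0.5) | 44% | 56% |
| Pooled residuals, t with 6 df | 25% | 39% |
| Pooled residuals, skew-normal | 37% | 51% |
| Each arm separately, normal | 18% | 32% |
| Each arm separately, gamma shape 12 (skewness 2/√12 = 0.58) | 41% | 56% |
| Each arm separately, t with 8 df | 35% | 47% |

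The pooled-residual rows rest on 1,000 trials each and the per-arm rows on 600. A further run of 1,000 trials with normal data and 5 imputations gave 23% for the per-arm check and 13% for the pooled one, so the figures depend on set-up.

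They measure disagreement between diagnostics, not wrong conclusions. Trials with both mixed per-arm verdicts and opposite conclusions from the unequal-variance t and Mann-Whitney tests (observed data, one-sided 0.05) were 0.5% to 1.0% under the null and 1.5% to 3.0% at the planned 5.5 points.

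**The case against.** The other side has several good arguments.

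- **Imputation.** A reader might infer that the rule cannot be followed at all once data are imputed. The article does not support that. One check on the observed changes gives one verdict, and where to check is a detail that an article may leave to the analysis plan. What stands is conditional: if the checks are repeated in each imputed dataset, there is no unique answer. The pooling problem for a rank p-value remains wherever the check is made.
- **Variance branch.** A reader might infer that switching on unequal variance also changes the null. If the paired test is a slip for a two-sample test on change, which is how the sample size section reads, pooled t to unequal-variance t keeps the null of equal means. Only the non-normality branch leaves it.
- **Transformation.** Signed changes cannot be log-transformed, but the article does not name a log, and other transformations of signed data exist. Nothing rests on this.
- **Rank tests.** They can gain power when tails are heavy, and if the treatment acts as a pure shift they answer nearly the same question. This is true. Normality is nevertheless not needed for a valid comparison of means at about 73 per arm, and the gain would come at the price of a target that depends on the data.
- **Remedy.** Baseline adjustment goes further than the defect strictly requires. That is fair, and a smaller change is therefore offered below.

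**Conclusion.** The point holds in a limited form and should be fixed. The article states a rule under which the observed data select the primary test, and one branch abandons the mean difference that the sample size section targets. The equal-variance condition is misplaced as written.

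The main harm is analyst discretion over the primary result and a possible change of target. The type I error effect is about 1 percentage point and appeared only when the arms differed in shape. With the same shape in both arms the rule stayed at 5.0% to 5.4%. These figures rest on an assumed diagnostic, assumed distributions and a two-sample reading of the default test.

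Two stronger readings should be resisted. One is that the trial has no defined primary target. The Abstract and the sample size section fix the endpoint, the contrast between arms and the 5.5-point difference in mean change, and it is the fallback that is open. The other is that the disagreement rates in the working measure the chance of a wrong result. They do not, and the share of trials with mixed verdicts and opposite conclusions was at most 3.0%. That a paired test does not compare the arms is a separate matter, not argued here.

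**What to change.** Remove the normality and variance checks as gates on the primary test, and prespecify one between-arm analysis of the mean. Regress 3-month HEI on arm and baseline HEI with heteroscedasticity-robust standard errors, fit it in every imputed dataset, and pool the arm coefficient and its variance by the usual rules. The robust errors take over the job of the variance check, and the coefficient stays in HEI points.

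At minimum, name one fixed unequal-variance two-sample t-test on HEI change, pooled in the same way.

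Report any rank-based comparison only as a sensitivity analysis, naming the test and saying how it is handled under imputation.

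The cost is wording. Baseline HEI is already collected and no participants are added. Planned power is kept, since even the unadjusted fixed t-test has 80.0% against 80.3%. The one real concession is a possible small loss of power relative to a rank test if the changes turn out heavy-tailed.

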### Intervention

Following baseline testing, participants will be randomized to one of two virtual intervention groups using a 1:1 ratio (nutrition intervention; *n* = 90 or contact control; *n* = 90) using blocked randomization with a 1:1 allocation ratio. Randomization is not stratified. The randomization allocation, generated by the study statistician, will be implemented using the Randomization module within the study database in VA REDCap. The Randomization module within REDCap prevents all users from viewing the treatment assignment of future study participants. This will ensure that all study personnel are blinded to treatment assignment prior to randomizing each participant.

The study coordinator will work with participants individually to ensure technology access and increased comfort level using the virtual platform. Devices and/or internet access will be provided to participants who report this as a barrier to participation. For both the nutrition intervention and contact control groups, we will enroll up to 15 participants into each virtual class cohort and run multiple different group sessions.

We will define successful adherence as completion of > 80% of all class sessions by the majority of participants. Length of time required for each educational session as well as modifications to the sessions will be tracked according to the Core functions and forms framework [35]. The core functions of the nutrition education protocol include 1) each session is led by a trained facilitator, 2) each session follows a standardized lesson plan, 3) each session concludes with question and answer opportunities with participants, and 4) each session is held in a group-based format. The “forms” are the specific ways in which each of the core functions are carried out when implemented under real world conditions and are modified to meet the needs of the local context and participants. For instance, standardized lesson plans may be adapted based on the cultural background of participants, and question and answer opportunities may include questions that are unique to a certain patient population (e.g., people with heart disease). All “forms” will be tracked by the class facilitator during each session to explore how the intervention should be tailored to meet participants needs and inform how other organizations may want to implement our nutrition program in the future.

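### The primary analysis tests raw change in HEI and the covariate list omits baseline HEI: valid between arms, but less efficient than ANCOVA

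*Protocol article*

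**What the plan says.** The abstract defines the endpoint: "The primary outcome is change in HEI score from baseline to 3 months". The Statistical methods section fixes the test: "The primary analysis will assess within-subject change in HEI score (3-month minus baseline) using a paired samples t-test". No covariate enters that test. The same section then lists what goes into the negative binomial regression models: "Covariates (age, race/ethnicity, sex, medical history/comorbidity, medications, education, living situation, and annual household income". Eight covariates or covariate groups are named, and baseline HEI is not one of them. Linear mixed effects models also appear among the modelling strategies, but they are not the primary analysis and their handling of baseline is not described.

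The Intervention section places randomisation after baseline testing and adds: "Randomization is not stratified". Table 3 schedules three dietary recalls at baseline and three at 3 months, so baseline HEI will be available as a pre-randomisation measurement.

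The Sample size and power section powers the trial on the difference in mean change: 73 per arm, a difference of 5.5, "with a standard deviation for both arms of 13.3", and "with a significance level (alpha) of 0.05 using a one-sided two-sample equal-variance z-test", giving 80.3%.

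**The concern.** When an outcome is measured before and after randomisation, subtracting baseline amounts to fixing the slope of 3-month HEI on baseline HEI at 1. HEI from three recalls carries day-to-day error, so with similar spread at the two times the true slope is below 1. Raw change then over-corrects for any chance difference between arms at baseline. Estimating the slope (ANCOVA) removes the excess and gives a smaller standard error for the same treatment contrast.

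What is at stake is precision in a trial planned with little margin: 80.3% power at one-sided 0.05. The plan proposes to adjust for demographic, social and medical covariates but leaves out the earlier value of the outcome itself.

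**Working it through.** **Inputs.** From Sample size and power: n = 73 per arm, difference 5.5, SD 13.3, alpha 0.05 one-sided. The 13.3 is read as the SD of change, because the sentence concerns mean changes. The correlation r between baseline and 3-month HEI is not in the documents and is assumed.

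**Step 1: reproduce the plan's figure.**
- Standard error = 13.3 × √(2/73) = 2.201, and 5.5/2.201 = 2.498.
- One-sided: Φ(2.498 − 1.645) = Φ(0.853) = 80.3%, as stated.
- Two-sided, same inputs: Φ(2.498 − 1.960) = Φ(0.538) = 70.5%.

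**Step 2: variance with baseline in the model.** With a common variance s² at both times:
- Var(change) = 2s²(1 − r)
- Var(ANCOVA) = s²(1 − r²)
- Ratio = (1 − r²)/[2(1 − r)] = (1 + r)/2, which is below 1 for every r below 1.

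**Step 3: power at 73 per arm**, with SD = 13.3 × √[(1 + r)/2]:

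| Assumed r | Variance ratio | SD | One-sided 0.05 | Two-sided 0.05 |
|---|---|---|---|---|
| unadjusted | 1 | 13.30 | 80.3% | 70.5% |
| 0.4 | 0.70 | 11.13 | 91.0% | 84.8% |
| 0.5 | 0.75 | 11.52 | 89.3% | 82.2% |
| 0.6 | 0.80 | 11.90 | 87.5% | 79.8% |
| 0.7 | 0.85 | 12.26 | 85.7% | 77.3% |
| 0.8 | 0.90 | 12.62 | 83.9% | 75.0% |

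These are normal approximations. For the two-sided ANCOVA column, the noncentral t, with one degree of freedom spent on baseline, gives values about 0.5 points lower. At r = 0.5 the gain is worth 73/0.75 = 97.3, or about 24 more completers per arm.

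**Step 4: the r needed for 80% two-sided.** Required ratio = [2.498/(1.960 + 0.842)]² = 0.795, so r = 2 × 0.795 − 1 = 0.59 or lower.

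**Step 5: sensitivity to unequal variances.** If the 3-month SD is k times the baseline SD, the ratio becomes k²(1 − r²)/(1 + k² − 2kr). With an assumed k = 1.2:
- r = 0.5: 1.44 × 0.75/(2.44 − 1.20) = 0.871, two-sided power about 76%.
- r = 0.7: 1.44 × 0.51/(2.44 − 1.68) = 0.966, two-sided power about 72%.

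The ratio reaches 1 only when kr = 1, that is, when the true slope is 1. It never exceeds 1.

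**Step 6: sensitivity to the meaning of 13.3.** If 13.3 were instead the SD of a single HEI score, two-sided power at r = 0.4, 0.5 and 0.7 would be 62.6%, 70.5% and 89.7% on raw change, and 77.8%, 82.2% and 93.8% with ANCOVA. The direction is the same.

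**The case against.** The strongest reply is that nothing here is wrong. Comparing mean change between randomised arms is unbiased, controls type I error, and matches both the stated endpoint and the quantity that was powered. That stands. A reader might infer from the unstratified randomisation that the estimate is biased. It is not: chance imbalance is already reflected in the standard error.

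A reader might also infer that adding baseline HEI would restore 80% two-sided power, or that omitting it caused the fall to 70.5%. The documents support neither. The first needs r of about 0.59 or lower under equal variances, and no r is given. The second confuses two issues: the fall comes entirely from replacing the plan's one-sided test with a two-sided one. Against its own one-sided test the plan has no shortfall.

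The size of the gain is indeed uncertain. It depends on r and on the ratio of the two SDs, and a larger 3-month SD could leave little of it. The plan's figures do argue against a very high r under equal variances. An SD of change of 13.3 implies a single-score SD of 13.3/√[2(1 − r)], which is 17.2 at r = 0.7 and 29.7 at r = 0.9, whereas a uniform spread over the whole 0 to 100 scale has an SD of only 28.9.

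Finally, the covariate list belongs to the secondary regression models, and an analysis plan that is not shown may say more. But the article does fix the primary test and does enumerate covariates, so the omission is stated text and not missing detail.

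**Conclusion.** The point holds as an efficiency weakness. The primary analysis as fixed ignores a pre-randomisation measurement that asymptotically cannot reduce precision. With equal variances, 13.3 as the SD of change and an assumed r between 0.4 and 0.7, power rises from 80.3% to between 86% and 91% one-sided, or from 70.5% to between 77% and 85% two-sided. With a 3-month SD 1.2 times the baseline SD, the two-sided figures fall to about 76% at r = 0.5 and 72% at r = 0.7, so the gain may be small. Whether the trial should use a one-sided test is a separate question, and this point does not depend on it.

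**What to change.** - Make the primary between-arm analysis a linear regression of 3-month HEI on arm with baseline HEI as covariate. Using change as the response gives the same arm coefficient, so the endpoint and its interpretation as a between-arm difference in change are unaltered.
- Let this model replace the paired t-test wording, which describes a within-subject test, so that the primary comparison is explicitly between arms.
- Add baseline HEI to the covariate list, and adjust each continuous secondary outcome for its own baseline value.
- Specify all of this before outcome data are analysed.

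The cost is one degree of freedom and a documented change to the analysis wording. No further participants, visits or measurements are needed, because baseline HEI is already scheduled.

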#### Dietary quality

The primary outcome of the study is dietary quality. To capture habitual dietary intake, participants will complete three 24-hr recalls [34] via the online Automated Self-Administered 24-hr (ASA24) Dietary Assessment Tool, developed by the National Cancer Institute, Bethesda, MD. Recalls will be collected for two week days and one weekend day within a two-week period. The dietary recalls will be used to calculate diet quality using the HEI; scores range from 0 to 100; higher scores indicate better adherence to the Dietary Guidelines for Americans.

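### The covariate-adjusted analysis of 3-month changes is assigned to negative binomial regression, a count model that cannot take signed change scores

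*Protocol article*

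**What the plan says.** All the modelling text is in the Statistical methods section of the protocol article.

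- The primary analysis is a t-test on "within-subject change in HEI score (3-month minus baseline", with unequal-variance, transformation and non-parametric fallbacks.
- After a sentence on exploratory post hoc work, the section lists the covariates (demographics, comorbidity, medications, social and economic factors). It says that they "will be included in negative binomial regression models, analyzing changes in outcomes from baseline to 3 months per participant". No other model is named in that sentence, and the baseline value of the outcome is not among the covariates.
- A later sentence covers the longer follow-up: "The same modeling strategies (negative-binomial regression, multinomial, or linear mixed effects models) will be applied to each outcome using piecewise approach". It does not say which outcome gets which model.

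The Dietary quality section describes the HEI: "scores range from 0 to 100; higher scores indicate better adherence to the Dietary Guidelines for Americans". The Sample size and power section plans the trial in HEI points: "the population difference in mean change in the two arms is µ1 - µ2 = 5.5", "with a standard deviation for both arms of 13.3".

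**The concern.** Negative binomial regression is a model for non-negative counts. The response named here is a difference between two scores, which can fall as well as rise. For HEI and the DEXA measures it is also not an integer. Sum scores such as the FGA, MPPT and FES-I change in whole numbers, but those changes are signed too.

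The adjusted analysis therefore cannot be carried out as written. An analyst who meets the failure must choose another model or alter the data, and would make that choice after seeing the data. Even a version that ran would, with the usual log link, give a ratio of mean changes, while the trial is planned on a difference in points.

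The sentence speaks of outcomes in general. The abstract defines most secondary outcomes (social isolation, loneliness, quality of life, physical function, body composition, fear of falling) as changes from baseline to 3 months, so these models are exposed as well.

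**Working it through.** **Inputs.** From Sample size and power: difference in mean change 5.5, SD of change 13.3 in each arm, 73 analysed per arm, and "significance level (alpha) of 0.05 using a one-sided two-sample equal-variance z-test". Assumed, because the document does not state it: the mean change in the control arm. I take 0 as the base case and show -2 to +10. Changes are taken as normal.

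**Step 1: reproduce the plan's own figure.** The standard error of the difference is 13.3 × √(2/73) = 2.201. Power = Φ(5.5/2.201 − 1.645) = Φ(0.853) = 0.803. This matches the stated 80.3%, so the 5.5 and 13.3 are the mean difference and SD of the change score as the plan uses them.

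**Step 2: share of negative HEI changes.** In each arm, P(change < 0) = Φ(−mean/13.3).

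- Control, mean 0: Φ(0) = 0.500.
- Intervention, mean 5.5: Φ(−5.5/13.3) = Φ(−0.414) = 0.340.
- Overall: (0.500 + 0.340)/2 = 0.42. Expected number: 73 × 0.840 ≈ 61 of 146.

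| Assumed control mean | Control below 0 | Intervention below 0 | Overall | Of 146 |
|---|---|---|---|---|
| -2 | 56.0% | 39.6% | 48% | 70 |
| 0 | 50.0% | 34.0% | 42% | 61 |
| +2 | 44.0% | 28.6% | 36% | 53 |
| +5 | 35.3% | 21.5% | 28% | 42 |
| +10 | 22.6% | 12.2% | 17% | 25 |

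At a control mean of +10, with the intervention arm at +15.5, about one participant in six still has a negative change.

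**Step 3: try the fit.** One data set was simulated with 73 per arm, control mean 0, intervention mean 5.5 and SD 13.3; 40% of its changes were negative. A maximum-likelihood negative binomial fit did not converge and returned undefined estimates. A generalised linear model with a negative binomial family stopped on an undefined deviance. Rounding the changes to integers gave the same two failures, so negative values alone are enough to break the model.

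**Step 4: the scale of the effect.** With a log link the arm effect is a ratio of mean changes. The same 5.5-point difference gives 7.5/2 = 3.75 at a control mean of +2, 10.5/5 = 2.10 at +5 and 15.5/10 = 1.55 at +10. It has no value at 0, where the ratio would be 5.5/0. The ratio therefore does not report the quantity on which the trial is planned.

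**The case against.** **The primary result is not touched.** This stands in full. The primary analysis is a t-test, and the 80.3% power comes from a comparison of mean changes. A reader might infer that the main conclusion or the sample size is at risk; the document does not support that.

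**The article names linear mixed models itself.** The piecewise sentence lists them and refers to the same strategies, which suggests that the authors had a menu in mind and condensed the earlier sentence. That is a fair reading of intent, and matching models to outcomes is often left to an analysis plan. But the 3-month sentence names one model only, nothing withdraws it, and the later list carries negative binomial regression forward without assigning it. An analysis plan would have to contradict the article, not merely fill it in.

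**The authors may have meant outcome levels.** The text says changes, per participant. Even for levels, a count model does not suit a bounded, continuous HEI score or DEXA fat mass.

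**Some outcomes are count-like.** This also stands. The number of affirmative food-security answers and the number of frailty criteria met are counts when analysed as levels, so count models need not be struck out altogether.

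**The size of the bias.** A reader might go further and calculate how far the effect would shrink: dropping negative changes would turn 5.5 points into 2.3, and setting them to zero would give 3.2 (both with a control mean of 0). The protocol proposes neither device, and these are differences between truncated or floored normal means, not negative binomial estimates. They do not measure an error in the plan.

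**Conclusion.** The point holds for the covariate-adjusted and secondary-outcome models. As stated, negative binomial regression cannot be fitted to changes from baseline to 3 months, because those changes are signed. With the protocol's own SD and difference, about 42% of HEI changes would be negative if the control arm does not change on average, and 17% to 48% for control means from +10 to -2. These shares rest on normal changes and on an assumed control mean. The conclusion itself needs only that some participants decline.

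This is a defect in a supporting analysis, to be corrected before the data are analysed. It is not a threat to the primary comparison or the sample size.

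**What to change.** In the covariate sentence, replace negative binomial regression for HEI and the other continuous or sum-score outcomes. Use a linear model of the 3-month score on arm, baseline score and the listed covariates, or a linear mixed model. Report an adjusted mean difference in points with a 95% confidence interval. The baseline score must be named explicitly: the present covariate list omits it, and regressing the 3-month score on that list alone would leave out adjustment for baseline.

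Keep negative binomial, multinomial or ordinal models only for named outcomes that are counts or categories, analysed as levels at each timepoint and not as signed changes. Make the same correction in the piecewise sentence by stating which model applies to which outcome.

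The cost is a wording change in the protocol, carried into any analysis plan. No new data and no change to the sample size are needed.
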